**Fig 1 pone.0282207.g001:**
[figure not shown]
Study design (CONSORT schedule). Flowchart of the different conditions of the Parfective Microtrial.

### Randomization

In this randomized, single-blinded, study on intervention heterogeneity, participants will be blinded to details until the end of the microtrial. Randomization (1:1) will occur through random selection of a participant number, linked to either the intervention or control condition. Participants will give consent prior to randomization (see Ethical clearance).

### Data collection/procedures

An overview of all measures and measurement occasions is given in Fig 2. All measures are widely used and found to be reliable and valid in terms of psychometric properties. Both the recruitment, as well as the data collection will be conducted in two separate cohorts in 2022/2023 and 2023/2024. The recruitment and pretest will start in October 2022 and 2023. Parents and children will be instructed to wear an Empatica E4 wristband at the university lab to measure their physiological reactivity, while receiving a 5–10-minute resting baseline session before the microtrial starts. Prior to the lab visit parents will be mailed questionnaires about their parenting practices, child behavior and environmental susceptibility. Parents will be instructed to bring the completed questionnaires with them to the university lab. Then, in the lab, parents will be observed interacting with their child. Following these baseline conditions, half of the parents will receive the “micro” parenting intervention—in the form of individual positive feedback concerning their parenting and their child’s behavior. Thereafter, at the same lab-session, parenting behavior will be observed again using the same interaction paradigm, after which we will re-administer to parents the questionnaires about their parenting and child behavior. Four weeks after the intervention we will re-administer the questionnaires about parenting and child behavior for the last time as follow-up assessment.

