**Methods:**

Participants are 120 families, with children aged 4–5 years, recruited from the community. Of these, 60 are randomly assigned to the “micro” intervention condition (i.e., immediate positive parenting feedback) and 60 families to the care-as-usual control condition. Assessments in both conditions will be conducted at baseline (pretest), after 2 weeks (posttest), and after 4 weeks (follow-up). Primary outcomes are the hypothesized moderating effects of physiology on the anticipated “micro” intervention effect (i.e., decrease in negative parenting behavior and/or increase in positive parenting behavior). Secondary outcomes are the observed (changes in) child behavior in response to the parenting intervention, such that those parents and children—in the same family—who manifest these physiological attributes will prove most susceptible to the beneficial effects of the intervention.

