## Materials and methods

### Design

The Parfective Microtrial is a randomized controlled microtrial with a “micro” intervention (i.e., immediate parenting positive feedback) and a control condition that tests physiologically-based differential susceptibility to changes in parenting. Participants are 120 families, with children aged 4–5 years, recruited form a community. Of those families, 60 will be randomly assigned to the “micro” intervention condition and 60 families to the control condition. After enrollment in the microtrial and randomization, the baseline assessment (pretest) will be carried out. The “micro” parenting intervention will be implemented after these baseline assessments. Participants in the care-as-usual control condition receive no immediate positive parenting feedback but will also be taken aside without their child, receiving only the instructions of the experiment. For the intervention condition, we will use an established parental self-efficacy microtrial intervention, which has been found to be effective in fostering parents’ positive parenting (ES = 0.63) and children’s positive behavior (ES = 0.64), by providing *immediate* positive feedback about one’s competence as a parent [10, 11]. Posttest and follow-up assessments will be conducted after 2 weeks and 4 weeks, respectively. The study procedure has been approved by the Ethics Review Board of Tilburg University.

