**Fig 2 pone.0282207.g002:**
[figure not shown]
SPIRIT schedule of enrolment, interventions, and assessments. Schematic representation of measures per timepoint.^a^ T1 –Pretest.^b^ T2 –Posttest (2 weeks after baseline).^c^ T3 –Follow-up (6 weeks after baseline).

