### Analyses

The data will be collected anonymously by assigning an ID number. Statistical analysis will involve several steps. First, using independent t-tests and/or alternative non-parametric tests, we will examine as a preliminary analysis whether randomization was successful, comparing baseline levels of demographics, parenting behavior and child externalizing behavior across the intervention and control condition. Possible significant differences at baseline will be used as covariates in analyses [47]. Latent change (LC) models in Mplus [48] will be used to test hypothesis H1-H3 on each dependent variable—parental self-efficacy beliefs, parenting behavior, child externalizing behavior and observed parenting and child behavior [49]. Because change is measured directly through latent difference variables, representing inter-individual differences in models are an excellent approach to examining repeated measures to estimate amount of change across time. In an LC model of parenting behavior and child behavior, behavioral change is cast as a latent variable, thereby separating measurement error. The mean of the latent difference variable is used as measure of mean differences between measurements, one to be predicted by other variables, including experimental condition (i.e., “micro” parenting intervention vs. control) and physiological scores. The Bonferroni correction is used to reduce chances of obtaining false-positive results (type I errors) [50].

### Hypothesis 1

◾ The feature of the LC model which evaluates this hypothesis links the “micro” parenting intervention (vs. control) with intervention responsiveness across pretest, posttest, and follow-up assessments, Specifically, the first model affords evaluation of group differences on the change from pretest to posttest and from posttest to follow-up. The second model affords evaluation of group differences from pretest to follow-up and from posttest to follow-up. Because the “micro” parenting intervention is focused on inducing parental self-efficacy beliefs, presumed to affect parents and children by changing their competence as a parent, we will also evaluate whether intervention effects are more pronounced when parents increase more rather than less in self-efficacy beliefs. We have four outcome measurements: reported and observed parenting change and reported and observed change in child behavior.

### Hypothesis 2

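### Posttest and follow-up times conflict across the protocol, and the text describes no follow-up observation to support the follow-up models planned for observed parenting and child behaviour

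*Protocol article*

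**What the plan says.** **Timing.** The abstract (Methods) states: "Assessments in both conditions will be conducted at baseline (pretest), after 2 weeks (posttest), and after 4 weeks (follow-up". The Design section gives the same intervals: "Posttest and follow-up assessments will be conducted after 2 weeks and 4 weeks, respectively". Neither names the starting point. The Fig 2 legend counts from baseline, with the posttest at 2 weeks and the last wave given as "Follow-up (6 weeks after baseline".

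Data collection/procedures describes a different sequence. Parents complete questionnaires at home, come to the lab and are observed, and half then receive the feedback. Next: "Thereafter, at the same lab-session, parenting behavior will be observed again using the same interaction paradigm". The sentence continues "after which we will re-administer to parents the questionnaires about their parenting and child behavior", with no interval. The final contact is: "Four weeks after the intervention we will re-administer the questionnaires about parenting and child behavior for the last time as follow-up assessment". No visit or mailing 2 weeks after the lab session is described.

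**Instruments by wave.** The Primary and Secondary outcomes sections give pretest, posttest and follow-up for the self-efficacy scale (GSPSEB), the parenting questionnaire (PBS-S) and the child behaviour questionnaire (ECBI). They give no occasions for the Crowell observations of parent or child. Table 1 lists observed parenting among the primary outcomes.

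**Models.** The Analyses section applies latent change models to every dependent variable, observed ones included. Under Hypothesis 1, the first model covers pretest-to-posttest and posttest-to-follow-up change. For the second: "The second model affords evaluation of group differences from pretest to follow-up and from posttest to follow-up". The same section adds: "We have four outcome measurements: reported and observed parenting change and reported and observed change in child behavior". Hypotheses 2 and 3 reuse this approach.

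**The concern.** Two things are at stake.

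First, a change score means little without its interval. An effect measured minutes after parents hear that they are among the most effective 20% is a different estimand from an effect 2 weeks later. Self-efficacy, reported parenting and observed parenting are all primary outcomes, so the ambiguity affects the main results, and the moderation tests in Hypotheses 2 and 3 inherit it. For questionnaires that ask how often something happens at home, the interval also decides whether a difference can be read as changed behaviour.

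Second, the observed outcomes are assigned models with changes up to follow-up, while the text describes no observation at follow-up. If there is none, the planned model for a primary outcome asks for quantities on which the trial collects no data.

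**Working it through.** The plan gives no figure to reproduce here. The check sets the sections side by side and then asks what each model can estimate.

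**Step 1. Stated times.**

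| Place | Posttest | Follow-up | Counted from |
|---|---|---|---|
| Abstract, Methods | 2 weeks | 4 weeks | not stated |
| Design | 2 weeks | 4 weeks | not stated |
| Fig 2 legend | 2 weeks | 6 weeks | baseline |
| Data collection/procedures | observation: same session; questionnaires: afterwards, no interval | 4 weeks | intervention |

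Take the lab visit as baseline and the unanchored times as counted from it. The pairs (posttest, follow-up) in weeks are then (2, 4), (2, 6) and, for the procedures text, (0 for the observation, 0 + 4 = 4). On that assumption follow-up is at 4 × 7 = 28 days or 6 × 7 = 42 days, a gap of 14 days.

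**Step 2. Can all sections be made to agree?** The legend puts follow-up at week 6 from baseline. The procedures put it 4 weeks after the intervention. Both hold only if the intervention is at week 6 − 4 = 2 from baseline. Baseline must then be the mailed questionnaires, completed 2 weeks before the lab visit. The 4 weeks in the abstract and Design must then count from the posttest (2 + 4 = 6), although the 2 weeks beside it count from baseline. No section states either point.

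On this reading the posttest (week 2) minus the intervention (week 2) is 0 weeks, so the posttest labelled as 2 weeks would measure an immediate effect. For the observations, pretest and posttest fall within one lab visit on this reading too.

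**Step 3. What the models can estimate.** Let a be the initial level, and let d12, d23 and d13 be the changes between waves 1, 2 and 3.

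- Model 1: y1 = a; y2 = a + d12; y3 = a + d12 + d23.
- Model 2: y1 = a; y3 = a + d13; y2 = a + d13 − d23.

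Each model has three unknown means. The rank of the matrix linking them to the observed wave means is:

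| Waves available | Model 1 | Model 2 |
|---|---|---|
| 1, 2 and 3 | 3 of 3 | 3 of 3 |
| 1 and 2 only | 2 of 3 | 2 of 3 |

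With two waves, Model 1 yields d12 but not d23. Model 2 yields only the combination d13 − d23, which is again d12. So 1 of the 3 stated intervals is estimable, and the two that end at follow-up are not. This applies to the two observed outcomes if they have two waves. GSPSEB, PBS-S and ECBI have three stated waves, and both models can be fitted to them whatever the spacing.

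**The case against.** The strongest reply is that the problem is narrower than it looks, and several parts of that reply stand.

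- **A reader might infer that the three-wave models cannot be run at all.** The documents do not support that. Three waves are stated for each questionnaire and both models are identified. For these outcomes the conflict leaves the interval undefined, not the model unestimable.
- **A reader might take it as settled that observed behaviour has no follow-up.** This is a strong inference, because the procedures name only questionnaires at the last contact and the outcome sections give occasions for the questionnaires but not for the observations. However, the procedures refer to Fig 2 for the measures at each occasion, and its grid is not available here. It may list a follow-up observation.
- **A reader might conclude that the posttest questionnaires are certainly same-session and therefore invalid.** The words about the lab session attach to the second observation; the questionnaires come after it with no stated place or interval. Same-session is the natural reading, since no later contact before the final one is described, but it is not explicit. Even if correct, it limits how the change is interpreted and is no reason to discard the wave. Discarding it would leave PBS-S and ECBI with two waves.
- **The 28-versus-42-day gap is conditional.** It disappears if baseline is the mailed questionnaire 2 weeks before the visit and the other 4-week figures count from posttest.

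What this reply does not remove is the contradiction in the readable text, legend included, or the mismatch between the described follow-up and the models assigned to observed outcomes.

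**Conclusion.** The point holds in two parts, and both should be corrected before recruitment.

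1. The assessment times contradict each other. The posttest lag is 0 weeks for the observation in the procedures and 2 weeks elsewhere; follow-up is at 4 or 6 weeks. The only reading that makes every section agree is unstated and places the posttest immediately after the intervention. The estimand of the pretest-to-posttest change is therefore not fixed.
2. As described in the text, observed parenting and observed child behaviour have two waves, while both Hypothesis 1 models need three. For these 2 of the 4 listed outcomes, the changes ending at follow-up cannot be estimated. This assumes that the Fig 2 grid shows no follow-up observation. The questionnaire models are not affected in this way.

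**What to change.** - Reconcile the abstract, Design, Data collection/procedures and the Fig 2 legend and grid into one schedule. State whether baseline is the mailed questionnaire or the lab visit, and give every interval from a named anchor.
- State the occasions for the Crowell observations in the outcome sections, as is already done for the questionnaires.
- Limit the models for observed parenting and observed child behaviour to pretest-posttest change, and drop follow-up claims for them, unless a follow-up observation is in fact scheduled. Carry the same limit into Hypotheses 2 and 3.
- Keep the three-wave models for GSPSEB, PBS-S and ECBI.
- State when the posttest questionnaires are completed. If it is in the lab session, interpret PBS-S and ECBI pretest-posttest change as an immediate change in report, and take pretest-to-follow-up as the contrast for reported behaviour change.

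The cost is protocol wording and, if there is no follow-up observation, fewer models to fit. Trial status says that no participant has yet been recruited, so no data are affected.

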**Fig 2 pone.0282207.g002:**
[figure not shown]
SPIRIT schedule of enrolment, interventions, and assessments. Schematic representation of measures per timepoint.^a^ T1 –Pretest.^b^ T2 –Posttest (2 weeks after baseline).^c^ T3 –Follow-up (6 weeks after baseline).

### Predictor

#### “Micro” parenting intervention

The experimental condition (i.e., “micro” parenting intervention vs. control) serves as predictor. All parents will come to the university lab with their child, while only half of them (1:1) receive individualized positive feedback concerning both their child and their parenting skills based on answers provided on the questionnaires completed at home. This approach has been used in other work, following ethics’ approval, and found it to be acceptable to parents—once they have been debriefed, as they will be about it at the end of the experiment. Specifically, an experimenter who self describes him/herself as a university researcher specializing in parent and child behavior will use a graph displaying “pseudo data” to compare what parents reported with responses provided by a non-existent group of parents; this presentation is designed to make parent and child look like they are doing well relative to others. Since self-efficacy beliefs (SEB) are based both on a self-evaluation that parents make about their skills and on their perception of their ability to positively influence their children [32, 33], the experimenter will emphasize the child’s positive development. All parents will be told the exact same thing: *“On the basis of the questionnaire filled out at home*, *we see that the way you behave with your child is particularly interesting for our research*. *We have noticed in earlier research we carried out that some childrearing practices*, *like yours*, *seem to be more effective in daily life*. *Based on an average calculated in earlier research with similar families in The Netherlands*, *we conclude that you are among the 20% of parents who seem to be the most effective with their children in three fields in particular*: *limit setting*, *emotion regulation and warmth”*.

The “micro” parenting intervention has been proven effective in two separate studies in fostering parents’ positive parenting and children’s positive behavior. Results showed that parents receiving positive feedback evinced more positive parenting (e.g., more positive affect towards their child) than non-reinforced parents in the control group; experimental children were more positive with their mothers (e.g., positive affect, enthusiasm towards task).

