#### Reported and observed parenting behavior

Reported parenting behavior will be assessed with the short version of the Parental Behavior Scale (PBS-S) at pretest, posttest and follow-up [42]. This questionnaire consists of 25 items and comprises five subscales: Positive parenting (e.g., “I make time to listen to my child, when he/she wants to tell me something”), Discipline (e.g., “When my child has been disobedient, I give him/her a chore as punishment”), Harsh Punishment (e.g., “I spank my child when he/she is disobedient or naughty”), Material Rewarding (e.g., “I give my child candy as a reward for good behavior”), and Rule Setting (e.g., “I teach my child to be polite at school”). A 5-point scale is provided for each item, ranging from 1 = (almost) never to 5 = (almost) always.

The Crowell Parent-Child interaction task procedure will be used to observe and rate parent behavior [43, 44]. Based on the Crowell procedure, the observation task takes 20 minutes to complete and consists of four episodes: warm-up, free play, frustration task, and recovery time. The parent scales are each internally consistent and well-defined conceptually. High internal consistency for each scale provides support for the reliability of the rating scale, and suggests that the Crowell scores can be useful as two separate scales measuring a child’s affective presentation and caregiver responsiveness, but also collectively as a total score assessing overall relational functioning (e.g., [45]).

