### Secondary outcomes

#### Reported and observed child behavior

One subscale assessing the degree to which child externalizing problem is a problem from the 36-item Eyberg Child Behavior Inventory (ECBI) will be used at pretest, posttest and follow-up—to assess the occurrence of reported child externalizing problem behavior [46]. This “Intensity” subscale measures frequency of externalizing behavior in children aged 2 to 16 years and has been shown to be a reliable (screening) instrument [3]. Example items are: “Does not obey house rules” and “Whines.”

Child behavior will be observed using the same interaction paradigm used to observe parent behavior [43, 44]. The parent and child scales of the Crowell procedure are each internally consistent and well-defined conceptually. As previously mentioned, high internal consistency for each scale provides support for the reliability of the rating scale, and suggests that the Crowell scores can be useful as two separate scales measuring a child’s affective presentation and caregiver responsiveness (e.g., [45]).

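### If the questionnaires are refilled in the session where parents are praised for them, PBS-S and ECBI change at that point cannot be told from re-rating and should not be read as behavior change

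*Protocol article*

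**What the plan says.** **Feedback.** Under the Micro parenting intervention heading of the Protocol article, half of the parents receive praise presented as resting on their own answers ("based on answers provided on the questionnaires completed at home"). A graph of invented data is used "to compare what parents reported with responses provided by a non-existent group of parents", and every praised parent hears one fixed script: "you are among the 20% of parents who seem to be the most effective with their children". The script names limit setting, emotion regulation and warmth, and the experimenter also stresses the child's good development. The Design section says that control parents are taken aside but get instructions only.

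**Order of events.** The Data collection/procedures section says that, once the feedback has been given, parents are watched with their child a second time before they leave the lab, "after which we will re-administer to parents the questionnaires about their parenting and child behavior". The questionnaires are given for the last time four weeks after the intervention.

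**Scales.** For the PBS-S: "A 5-point scale is provided for each item, ranging from 1 = (almost) never to 5 = (almost) always". For the ECBI, the Intensity "subscale measures frequency of externalizing behavior". Table 1 lists three primary measures (GSPSEB, PBS and observed Crowell parenting) and makes the ECBI and observed child behavior secondary.

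**Analysis.** The Analyses section applies latent change models to each dependent variable for H1 to H3, with a Bonferroni correction. Hypothesis 1 has one model for pretest to posttest and posttest to follow-up, and another for pretest to follow-up and posttest to follow-up.

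**Conflicting timing.** The Design section states: "Posttest and follow-up assessments will be conducted after 2 weeks and 4 weeks, respectively". The Abstract agrees with it. The Fig 2 legend puts T2 at 2 weeks and T3 at 6 weeks after baseline.

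**The concern.** The praise is directional, is given to one arm only, and is tied explicitly to the forms that the parent is about to complete again. The praised domains overlap with what the PBS-S scores (positive parenting, discipline, rule setting). Under the Data collection/procedures section, only the repeated interaction task comes between praise and refill, and that task takes about 20 minutes. How often a parent does something at home, or how often the child misbehaves there, cannot have changed in that interval. The rating of it can.

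A pretest-to-posttest arm difference on the PBS-S or ECBI would then be reported under H1 as better parenting or fewer externalizing problems when it could be re-rating alone. Because H2 and H3 use the same change variables, any moderation found on these two scales would carry the same ambiguity. A posttest-to-follow-up contrast that starts from the same-session score inherits it too: ratings that drift back after the visit would look like fading behavior.

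**Working it through.** **Step 1. Which outcomes are exposed?**

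| Measure | Status | What it records | Can it truly change within the session? |
|---|---|---|---|
| GSPSEB | primary | belief in own parenting ability | yes; it is the declared target |
| PBS-S | primary | frequency of parenting behaviors | no |
| Crowell, parent | primary | behavior observed in the lab | yes |
| ECBI Intensity | secondary | frequency of child behaviors | no |
| Crowell, child | secondary | behavior observed in the lab | yes |

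So one of the three primary measures and one secondary measure are affected. The Data collection/procedures section does not name the GSPSEB among the refilled forms, although its own section places it at posttest.

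**Step 2. Is the posttest really in the same session?** The Data collection/procedures section gives two refills: in the session, and four weeks after the intervention. The Fig 2 legend puts follow-up at 6 weeks after baseline. Then 6 − 4 = 2, so the intervention would fall in week 2, together with T2. These two places agree if baseline means the home questionnaires and the lab visit comes about two weeks later. The article does not say so. The Abstract and the Design section put follow-up at 4 weeks, which does not fit this reading. Same-session refill is therefore what the procedures describe, but it is not settled.

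**Step 3. Do the planned methods remove the problem?** Latent change models separate random measurement error. A shift common to one arm is not random error; it enters the mean of the latent difference as an effect of condition. Bonferroni limits chance findings and does not correct bias.

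**Step 4. Illustration of size.** The plan has no figure on this point to reproduce. Inputs from the Design and Recruitment sections: n = 60 per arm, two-sided α = .05. Assumed: no true change, and a pure reporting shift of δ SD in the praised arm. The probability of a significant result is that of a noncentral t with df = 2 × 60 − 2 = 118 and noncentrality δ√(n/2) = δ√30 = 5.477δ. The three-test Bonferroni divisor is also assumed (α = .05/3).

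| Assumed shift δ | Noncentrality | Significant at α = .05 | Significant at α = .05/3 |
|---|---|---|---|
| 0 | 0 | 5% | 1.7% |
| 0.2 | 1.10 | 19% | 10% |
| 0.3 | 1.64 | 37% | 22% |
| 0.4 | 2.19 | 58% | 41% |

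Adjusting for the pretest sharpens the bias rather than reducing it. With an assumed pre-post correlation of 0.7, the residual SD is √(1 − 0.49) = 0.714. A shift of 0.2 SD then acts like 0.2/0.714 = 0.28 and is significant in 33% of trials at α = .05; a shift of 0.3 SD is significant in 63%.

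**The case against.** The best defence has four parts.

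- **Self-efficacy is meant to move.** A reader might infer that two of the three primary outcomes can shift only as an artefact. The documents do not support that. The GSPSEB measures the belief that the feedback is designed to raise, and H1 predicts the rise. A shift is a legitimate mechanism effect, though not evidence of changed parenting. This part stands in full.
- **The posttest may come two weeks later.** The Abstract, the Design section and the Fig 2 legend all give 2 weeks. If families do complete the posttest after two weeks at home, frequency could have changed and the strong form of the point falls away. This stands as a condition. A weaker form remains, because the Randomization section keeps participants blinded to details until the end and debriefing comes only then, so the praise may still color self-report.
- **Part of the protection is already planned.** Observed parenting is a primary outcome, reported and observed change are kept separate, and a pretest-to-follow-up contrast exists. That is so, but nothing gives the observed outcome priority or stops a same-session PBS-S result from supporting H1 alone.
- **The size is assumed.** That is correct; the percentages are illustrations.

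Two further inferences go beyond the documents. One is that a same-session difference *is* re-rating: it cannot be distinguished from re-rating, which is a different statement. The other is that the physiological moderators would really be picking up suggestibility: nothing in the article links skin conductance or heart rate to that.

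**Conclusion.** The point holds in a limited form and should be acted on. If the order of events in the Data collection/procedures section governs, pretest-to-posttest change on the PBS-S and ECBI cannot support a conclusion about parenting or child behavior, and the planned models and multiplicity correction do not help. It concerns one of three primary measures and one secondary measure; it does not extend to the GSPSEB or to the Crowell observations, and it does not invalidate the trial. It depends on the same-session reading, which conflicts with the 2-week posttest given elsewhere. The extent of any false conclusion is unknown. Assumed shifts of 0.2 to 0.4 SD give 19% to 58% significant results at α = .05, or 10% to 41% with an assumed three-test correction.

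**What to change.** 1. Reconcile the timing of posttest and follow-up across the Abstract, Design, Data collection/procedures and the Fig 2 legend, and state when each questionnaire is completed relative to the feedback.
2. Rest the conclusion on immediate parenting change on observed Crowell parenting, which is already collected before and after the feedback.
3. Treat same-session GSPSEB as a manipulation check or mechanism measure.
4. For the PBS-S and ECBI, use the already planned pretest-to-follow-up contrast, or a posttest that truly follows time at home. Do not interpret same-session change, or posttest-to-follow-up change that starts from it, as behavior change.
5. Label PBS-S and ECBI results as *reported* and state that they cannot alone support a claim of behavior change, since parents are not debriefed until the end.

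The cost is an order of priority among outcomes and one analysis rule; no new data are needed, and the article says that no participant had yet been recruited. The losses are that same-session PBS-S and ECBI scores give up confirmatory status, and that a Crowell-led conclusion covers immediate change only, because the procedures list only questionnaires at four weeks. Follow-up self-report stays partly exposed to the praise. The article states masking for participants only, so the Crowell ratings will carry this weight best if raters do not know the arm.
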